### Economic evaluation and cost analysis

Total-body CT scanning will be evaluated economically from a societal perspective against a conventional diagnostic strategy consisting of X-ray, FAST and selective CT scanning according to the ATLS guidelines. Cost-effectiveness analyses will be performed with the costs per patient alive and costs per patient alive without serious morbidity as outcome measures. Additionally, a cost-utility analysis will be done with the cost per QALY as outcome measure. Incremental cost-effectiveness ratios will be calculated, expressing the extra costs per (i) extra patients alive, (ii) extra patients alive and without serious morbidity, and (iii) additional QALY. Sampling variability will be accounted for by (bias-corrected and accelerated) non-parametric bootstrapping. Sensitivity analyses will be directed at applied QALY algorithms (generic, country-specific; uniform, linear, curvilinear interpolations between measurements), unit costs of major cost components, and the (country-specific) friction period in case of production loss. Subgroup analyses will be performed by the predefined subgroups. The time horizon for the cost-effectiveness analysis will be six months following trauma. Because of this time horizon, no discounting will take place.

The economic evaluation will take all direct and indirect medical and non-medical costs into account. The direct and indirect medical costs include the costs of initial trauma care, ICU-care and care at the general ward during the index admission - including all diagnostic and therapeutic procedures - as well as the costs of repeat hospital admissions, other intramural care like rehabilitation and extramural care during the first 6 months post trauma. Direct and indirect non-medical costs of, respectively, out-of-pocket expenses and production loss during the first 6 months will also be estimated. Volume data will be collected by case report form, institutional administrative databases and by patient questionnaires at 3 and 6 months, depending on the cost category. The patient questionnaire will be derived from the Dutch Health and Labour Questionnaire and adapted for international use. Unit costing will be based on activity based costing and hospital ledger data concerning the major diagnostic procedures in this trial. Unit costing of other health care components will be based on available national guidelines. In case of absence of national guidelines in specific countries, available unit costs from abroad will be recalculated using Organisation for Economic Co-operation and Development (OECD) purchasing power parities. Out-of-pocket expenses will be estimated as supplied by the patients. Indirect costs of production loss will be calculated according to the Dutch perspective by following the friction cost method, while applying the most recent friction cost period known at the time of analysis. Costs will be calculated for the base year 2012. Unit costs of other base years will be price-indexed.

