### Endpoints

The primary outcome criterion for this trial is in-hospital mortality.

As secondary parameters for the trial focus on additional clinical consequences for the patients and cost-effectiveness and cost-utility:

- mortality (24-h, 30-day and 1-year mortality);

- morbidity (complications and total number of (re-)interventions and re-admissions up to 6 months post trauma; transfusion requirements, length of ICU stay and number of ventilation days);

- several time intervals during initial evaluation (time of arrival, time to CT, scanning time, time to diagnosis and time in the ED);

- radiation exposure;

- quality of life 6 and 12 months after the trauma as recorded by completing the EuroQol-6D;

- general health 6 and 12 months after the trauma as recorded by completing the HUI-3;

Economic parameters/endpoints:

- total costs of imaging during the initial/index hospital stay;

- total direct and indirect medical and non-medical costs during the first half year posttrauma;

- quality adjusted life-years (QALY's).

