### Sample size calculation and data analysis

A previous study reported a reduction in mortality from 15% to 8.6% with total-body CT scanning as the single diagnostic procedure during trauma evaluation as compared to historical control data [29]. Analysis on the large German polytrauma registration database performed by Huber-Wagner et al. showed a significant reduction in the 24-h mortality in patient who underwent immediate total-body CT compared to the conventional group (10% vs. 12%, P = 0.038) [25]. Historical AMC data show a mortality rate of 12% for trauma patients matching the current trial inclusion criteria. Based on the combination of the AMC data and the participation of the other trauma centers with comparable trauma populations, it is expected to find a reduction in mortality from 12% to 7%. The detection of such a difference requires 539 patients per group using a power of 80% and a two-sided alpha of 5%. Based on the historical and estimated data of the participating centers the inclusion period will take about 1,5 years and the follow-up period will take an additional year.

The main analyses of primary and secondary outcomes will be conducted for all randomized patients according to the result of the randomization (intention-to-treat). Data are expressed as percentages for categorical data, as mean and standard deviation (SD) for normally distributed numerical data and as median, range, and, where appropriate, inter-quartile range (IQR = 25 to 75%) for non-normally distributed numerical data.

The following subgroups will be used for subgroup analysis:

- multitrauma patients (defined as Injury Severity Score (ISS) >/=16);

- severe traumatic brain injury patients (defined as admission Glasgow Coma; Scale (GCS) ≤ 8 and an Abbreviated Injury Score (AIS)-head of ≥ 3);

- penetrating versus blunt trauma.

A p-value less than 0.05 is considered statistically significant. If appropriate, predictive values between variables are calculated. Predictive values in continuous outcome variables are assessed using a multivariate regression model, and binary outcome measures are assessed using a multivariate logistic regression model. In case of binary outcome measures, predictive values are expressed as Odds Ratio's (OR) with 95% Confidence Intervals (CI). Data are analyzed using the Statistical Package for the Social Sciences (SPSS) version 18.0 SPSS Inc., Chicago, IL.

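### Six-month horizon caps each averted death at half a QALY in the cost-utility ratio, with no horizon sensitivity analysis although outcomes run to 12 months

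*Protocol article*

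**What the plan says.** In the protocol article, Economic evaluation and cost analysis, the horizon is fixed: "The time horizon for the cost-effectiveness analysis will be six months following trauma". The next sentence adds: "Because of this time horizon, no discounting will take place". Three ratios are planned. Two come first: "Cost-effectiveness analyses will be performed with the costs per patient alive and costs per patient alive without serious morbidity as outcome measures". The third follows: "Additionally, a cost-utility analysis will be done with the cost per QALY as outcome measure". The sensitivity analyses are also listed: "Sensitivity analyses will be directed at applied QALY algorithms (generic, country-specific; uniform, linear, curvilinear interpolations between measurements), unit costs of major cost components", and then the friction period. The horizon is not among them.

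Costs are collected for the first half year only (Endpoints; Economic evaluation and cost analysis), with patient questionnaires at 3 and 6 months. Outcomes run longer. Endpoints lists "mortality (24-h, 30-day and 1-year mortality") and "quality of life 6 and 12 months after the trauma as recorded by completing the EuroQol-6D".

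The hypothesis is in Sample size calculation and data analysis: "it is expected to find a reduction in mortality from 12% to 7" (per cent), with in-hospital mortality as the primary outcome.

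**The concern.** A strategy whose expected benefit is early deaths averted has a particular time profile. Index admission, intensive care, readmission and early rehabilitation fall largely inside six months, while almost all the life-years gained fall after it. A cost-per-QALY ratio cut at six months therefore counts much of the cost of producing extra survivors and at most half a year of what they gain.

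The ratio is valid as a six-month quantity. The risk lies in how it is read. A reader who sets it beside cost-per-QALY figures from longer horizons could judge the strategy poor value because of the cut-off, and no planned analysis would show how far the figure depends on it.

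**Working it through.** **Inputs from the protocol.** Mortality 12% and 7%, difference d = 0.05; 539 per group, 80% power, two-sided 5%; horizon 0.5 year; mortality and utilities to 1 year; lifetime cancer mortality of about 0.08% per total-body CT (Discussion).

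**Inputs assumed, because the protocol gives none.** Survivor utility u = 0.6, constant over time; six-month incremental cost C = 1,000 per patient; annual cost c per extra survivor after month six, from 0 to 40,000; 20 or 30 remaining years discounted at 3%. Averted deaths are placed at time zero and the survivors live to the end of each horizon.

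**Step 1: the plan's own figure.** With pooled variance, n = [1.960 x sqrt(2 x 0.095 x 0.905) + 0.842 x sqrt(0.12 x 0.88 + 0.07 x 0.93)]^2 / 0.05^2 = 539 per group, as stated. The planned effect is 539 x 0.05 = 27 deaths averted per group of 539.

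**Step 2: QALY ceiling (utility 1).**
- Six months: 0.5 per averted death; 0.05 x 0.5 = 0.025 per patient.
- Twelve months: 1.0 per averted death; 0.05 x 1 = 0.05 per patient.

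The doubling needs no assumed cost, and no particular utility as long as it is constant.

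**Step 3: cost per QALY.** For a horizon of L (discounted) years,

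R(L) = [C + d x c x (L - 0.5)] / (d x u x L).

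At six months R = 1,000 / (0.05 x 0.6 x 0.5) = 1,000 / 0.015 = 66,667, whatever c is. L is (1 - 1.03^-20)/0.03 = 14.88 for 20 years and 19.60 for 30 years.

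| Horizon | c per year | Calculation | R | Six-month R divided by this R |
|---|---|---|---|---|
| 12 months | 0 | 1,000 / 0.03 | 33,333 | 2.0 |
| 12 months | 10,000 | 1,250 / 0.03 | 41,667 | 1.6 |
| 20 years | 0 | 1,000 / 0.446 | about 2,240 | 29.8 |
| 20 years | 10,000 | (1,000 + 500 x 14.38) / 0.446 | about 18,300 | 3.6 |
| 20 years | 20,000 | (1,000 + 1,000 x 14.38) / 0.446 | about 34,500 | 1.9 |
| 30 years | 0 | 1,000 / 0.588 | about 1,700 | 39.2 |

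**Step 4: where the direction turns.** Setting R(L) equal to R(0.5) gives c = C / (d x 0.5) = 1,000 / 0.025 = 40,000 a year for any L. Put differently, c/u = 40,000 / 0.6 = 66,667, the six-month ratio itself. Above that, a longer horizon makes CT look worse. If C is zero or negative and mortality is lower, CT already dominates at six months.

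**Step 5: late radiation harm.** Suppose 0.08% mortality costs 10 to 30 life-years each and the control arm receives no radiation at all. The loss is 0.0008 x 10 = 0.008 to 0.0008 x 30 = 0.024 QALY per patient, against 0.05 x 20 = 1.0 gained over 20 years (both undiscounted, utility 1). It does not reverse the direction.

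**The case against.** **Only one ratio of three is affected.** Cost per patient alive and cost per patient alive without serious morbidity come first in the plan, and they count an averted death in full. This stands. Study objectives contains no economic objective, and Endpoints places cost-utility among the secondary parameters, so it would be wrong to say that an objective of the trial is compromised.

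**A reader might infer a built-in bias against total-body CT.** The documents do not support that. The truncation works against whichever arm has lower mortality, and it vanishes if mortality is equal. On the ratio scale it also needs a positive incremental cost and later survivor costs below the break-even in step 4.

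**A reader might take the 30- to 40-fold lifetime gap as the size of the error.** It rests on assumed utility, cost, life expectancy and discount rate, and above all on zero cost after month six. At 10,000 a year it falls to about 3.6-fold. Production loss should not be added as a one-sided cost of survival either: the friction method limits it, and nothing in the text exempts deaths from it.

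**A reader might infer that the trial will conclude CT is not cost-effective, or that the 12-month data are thrown away.** The protocol states no threshold or decision rule. The horizon sentence names the cost-effectiveness analysis, and the planned interpolation between measurements could be read as using the 12-month utility. But all costs stop at six months, and discounting is dropped because of that horizon. Six months for all three ratios is the natural reading, though not an explicit one.

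**A within-trial horizon matched to cost collection is a coherent choice, openly stated.** True, and it is the reason to keep the six-month result. It does not explain why the horizon is missing from a list of sensitivity analyses that is otherwise specific, when outcomes to 12 months are at hand.

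**Conclusion.** The point holds in a conditional form. Under the trial's own hypothesis the six-month cost-utility ratio credits at most 0.025 QALY per patient for survival, half the ceiling that the planned 12-month outcomes would allow. This part follows from the protocol's own figures.

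Whether the ratio is then unfavourable to CT depends on three conditions: lower mortality with CT, a positive six-month incremental cost, and later survivor costs per unit of utility below the six-month ratio. If they hold, the overstatement is up to about 2-fold against 12 months (about 1.6-fold at an assumed 10,000 a year per survivor). Against a lifetime horizon no single factor can be given from the documents.

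The primary analysis and the two ratios per patient alive are not touched by this ceiling. The label is a cheap improvement: it changes what the cost-utility result can be used to conclude.

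**What to change.** In Economic evaluation and cost analysis:

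1. Keep the six-month cost per QALY, label it a short-term result, and state that six months applies to the cost-utility ratio as well.
2. Pre-specify a 12-month cost-utility analysis using the 1-year mortality and 12-month utilities already collected. Extrapolate costs for months 6-12 from the 3-6 month rate and vary them over a stated range.
3. Add a discounted longer-horizon scenario that includes survivors' later costs and the late radiation risk, and report the later survivor cost at which the direction turns.
4. State that CT will not be judged not cost-effective per QALY from the six-month ratio alone.

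The cost is analysis time and a few sentences, with no new data collection. Asking costs again at month 12 is less attractive: inclusion began in April 2011 and the article appeared in March 2012, so the first patients were already close to that visit and some would be missed. The downside is that costs after month six and the longer-horizon survival and utility rest on assumptions. These results therefore belong beside the six-month figure, with their ranges shown.

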### Safety monitoring

An independent Data and Safety Monitoring Board (DSMB), consisting of three members (2 physicians and 1 clinical epidemiologist), is installed for this trial. On regular intervals, this committee will review accumulating trial data and provide advice on the conduct of the trial to the trial leader and Steering Committee. The DSMB will focus both on safety and effectiveness data. Standard Operating Procedures (SOP) will be used with respect to the schedule and format of DSMB meetings and with respect to the format and timing of presenting data. The DSMB can recommend the Steering Committee to terminate the trial when there is clear and substantial evidence of harm.

#### Safety and efficacy monitoring

The role of the DSMB is to perform an interim review of the trial's progress including updated figures on main outcomes and safety data. This review would include, but not be restricted to, the following:

• monitor compliance with the protocol by participants and investigators;

• monitor evidence for treatment differences in the main efficacy outcome measures;

• monitor evidence for treatment harm (e.g. SAEs, deaths);

• decide whether to recommend that the trial continues to recruit participants or whether recruitment should be terminated either for everyone or for some treatment groups and/or some participant subgroups;

• suggest additional data analyses;

• monitor compliance with previous DSMB recommendations;

• consider the ethical implications of any recommendations made by the DSMB;

• assess the impact and relevance of external evidence as supplied by the Chief Investigator.

The DSMB will evaluate these safety and efficacy parameters at regular intervals. After 275 (25%), 550 (50%) and 700 (65%) included patients, non-blinded interim-analyses for evaluation of safety rules will be performed. No formal stopping rules based on statistical criteria alone will be used. The DSMB decides after evaluation of all necessary interim data whether the trial will be continued or terminated. Other investigators, designated by the Board of Direct of the AMC to control the trial will have the authority to gain insight in all the confidential data relevant for the trial as well.

### Ethics

This trial is conducted in accordance with the principles of the Declaration of Helsinki [30], the Medical Research Involving Human Subjects Act (WMO) and 'Good Clinical Practice' guidelines. The Medical Ethical Committee of the Academic Medical Center in Amsterdam has approved the protocol on January 6 2011. The Ethical Committees of the participating centers approved for local feasibility.

To participate in a research project the subjects must be volunteers and informed participants according to ethical principles stated in the Declaration of Helsinki. However, the acute life-threatening situation of severely injured trauma patients hinders a considered decision. Neither a legal guardian nor a legal representative of the patient can make a decision because of the time pressure or because they simply do not arrive in time. A temporary waiver of informed consent during randomization and the consecutive diagnostic phase during trauma survey was approved by the Medical Ethical Committee of the Academic Medical Center in Amsterdam. In all cases informed consent will be asked afterwards from the patient or the legal guardian/representative of the patient, as soon as reasonably possible.

## Discussion

The need for prospective studies to measure the effect of immediate total-body CT scanning in trauma care has been stressed recently by several authors [8,22,23,25,29]. Retrospective studies have shown the possible benefits in time and outcome of immediate total-body CT scanning in trauma patients. The next step is to compare its usage to the current best imaging strategy according to ATLS guidelines in a prospective trial.

The primary question that needs to be answered is whether immediate total-body CT scanning in severely injured trauma patients decreases mortality and significant morbidity when compared to conventional imaging strategies supplemented with CT. Therefore, randomization is within the hospital, ensuring that a comparison between imaging protocols is made per hospital instead of between hospitals. The design of the trial is multi-centered, with participating centers in The Netherlands, Switzerland and North America. This design assures that differences in trauma populations, trauma mechanisms and workflow in different parts of the world are taken into account as well. This is important to make sure that if an effect on outcome is seen that this can solely be attributed to the usage of a total-body CT scan.

The in- and exclusion criteria assure that only potentially severely injured trauma patients are included and over triage is minimized. Especially severely injured patients are thought to benefit the most from fast and detailed information that becomes available with total-body CT scanning. Selecting the right patients for immediate total-body CT scanning is therefore crucial. Since the excluded trauma patients will be registered as well, final analysis will show whether the chosen inclusion criteria led to an appropriate selection of patients. Furthermore, severely injured patients are those patients in whom the radiation dose may be justifiable since their possible life-threatening injuries require accurate treatment as fast as possible. Trauma patients are exposed to a great amount of radiation and it is well known that CT scanning is a significant contributor to iatrogenic radiation exposure [31]. The mean effective dose received by trauma patients evaluated by conventional imaging protocols supplemented with CT scanning was found to be 22.7 milliSievert (mSv) [32]. A single total-body CT scan accounts for 14-21 milliGray (mGy), which in medical X-ray studies is equal to mSv [31]. However, cumulative doses for all the radiological examinations undertaken during hospitalization may be much higher [33]. The long-term effects of the radiation exposure are based upon estimations, but the most concerning is an increased cancer risk. For a single total-body CT examination the estimated lifetime attributable cancer mortality risk is thought to be around 0.08% [31].

After conventional imaging in terms of X-rays and ultrasound has been finished the trauma leader has to decide whether or not selective CT should take place. The ATLS guidelines provide some decision rules but to some extent it is susceptible to individual judgment. Experience of the trauma leader and local infrastructures may influence these decisions. Furthermore, the randomization between total-body CT and conventional imaging supplemented with CT within each center holds the risk of a learning curve experienced by trauma leaders. If the trauma leader suspects detecting more injuries with a total-body CT scan than was expected on clinical grounds, performing selective CT scanning in the conventional arm could become more easily accessible and may lower the possible differences in outcome between the study groups. That is why the indication for selective CT scanning in the conventional arm are pre-defined, based on combined local protocols of the participating centers. The standardization of the conventional arm will lower the aforementioned risks.

This trial aims to determine the optimal diagnostic strategy for severely injured trauma patients in the ED. If immediate total-body CT scanning is found to be the best imaging strategy in severely injured trauma patients it could replace conventional imaging supplemented with CT in this specific group. This will probably minimize the total diagnostic work-up time of the initial trauma evaluation. How this reflects in outcome needs to be analyzed in this trial. Furthermore, severely injured patients are already likely to receive selective CT scanning after conventional imaging according to ATLS guidelines or according to local trauma protocols. Segmented CT scanning in these patients, added to the conventional work-up, will result in a high total radiation dose because of overlapping radiation fields. It could therefore even be possible that an immediate total-body CT results in a lower the total effective radiation dose compared to the conventional work-up with selective CT scanning [27].

The trial not only focuses on clinical outcome in terms of mortality and morbidity. Since radiation exposure and cost-effectiveness will be taken into account as well, the REACT-2 trial will provide a detailed overview of considerations that should be taken into account when discussing the efficacy of immediate total-body CT scanning in trauma patients. The large sample size will make sure that results are reliable and can be generalized to all international trauma populations and centers.

